### Subgroup analysis

We will compare the effects of the sheets on PrepDM scores in people with chronic pain vs acute pain, and in people with higher pain intensity vs lower pain intensity. We will also examine effects on healthcare intentions in people who received the fact sheet through GP-led approach vs patient-led approach.

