### **Procedure**

Participants will be people >18 years visiting their GP for back pain who receive a back pain fact sheet and who choose to complete the online survey. Patients who access the survey link and agree to participate in the study will provide clinical and demographic details via an online form (age, sex, ethnicity, duration of back pain, pain intensity). No data from a participant's medical record will be used in this study.

COPYRIGHTED MATERIAL REDACTED

**Figure 3.** Potential participants can access the survey via a QR code on printed/emailed sheet or via clickable link on the fact sheet page or via social media advertisements.

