## Statistical analysis

Our primary analysis will compare the PrepDM scores in people exposed to the JAMA fact sheet vs the ACHSQ fact sheet, immediately after they have read the sheet. Assuming a mean difference of 6 points on a 100-point scale (ie 60 points in JAMA fact sheet group, 54 points in ACHSQ group, SD of 26) with 90% power, we require a sample size of 790. To account for anticipated uneven group size we will increase the minimum sample size to 1000.

For the secondary outcomes of management intentions, reassurance, and acceptability, we compare means and proportions where applicable in the whole sample and generate 95% confidence intervals.

---

 Western Sydney University. Human Research Ethics. Guidance on Reimbursements. 2020.

 Dhand, N. K., & Khatkar, M. S. (2014). Statulator: An online statistical calculator. Sample Size Calculator for Comparing Two Independent Means. Accessed 8 May 2023 at <http://statulator.com/SampleSize/ss2M.html>

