#### Subgroup analysis

We will conduct a planned subgroup analysis to examine healthcare intentions in people who received the fact sheet through GP-led approach vs patient-led approach, people with chronic pain vs acute pain, and in people with high pain intensity ( $\geq 6/10$ ) vs lower pain intensity.

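### The pain-intensity subgroup analysis of PrepDM splits participants into higher and lower with no cut-point; an interaction on the full score would use the data better if effect modification is near-linear

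*Supplement*

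**What the plan says.** In the latest protocol version (the one with three access routes), the Subgroup analysis section plans to compare the effects of the two sheets on PrepDM, the primary outcome, by acute versus chronic pain and "in people with higher pain intensity vs lower pain intensity". It does not say where higher begins, how pain is scored, or what model or test compares the effects. The updated Statistical methods / analysis field of the registry record uses the same wording.

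The Procedure section lists what participants report on the online form: "age, sex, ethnicity, duration of back pain, pain intensity". No response format is given for pain intensity.

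The only threshold in the supplement is in a superseded protocol version, the one with PrepDM as primary outcome but only two access routes: "in people with high pain intensity ( $\geq 6/10$ ) vs lower pain intensity". There it applied to healthcare intentions, not PrepDM, and the latest version does not carry it over. No separate analysis plan is shown.

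**The concern.** The question is whether the difference between the sheets changes with pain intensity. Cutting a graded measure into two groups treats everyone on one side of the cut as alike. If the effect changes gradually with pain, the contrast is estimated less precisely than the collected data allow.

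Because the current text names no cut, the groups cannot be formed without a further decision, and nothing shown requires that decision to precede sight of the outcomes. At stake are the precision of this subgroup result and, if the cut were picked by its result, its false-positive rate.

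**Working it through.** **Inputs from the plan** (Statistical analysis). The design effect is 6 points on the 100-point PrepDM scale. The spread, power and resulting total are given as "SD of 26) with 90% power, we require a sample size of 790". The team then raises the target to at least 1000 in view of "anticipated uneven group size".

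**Assumptions.** Two-sided alpha 0.05, which is not stated for the primary analysis but fits the plan to "generate 95% confidence intervals" for secondary outcomes. Equal arms. A numeric pain score.

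**1. The plan's own figure.** n per arm = 2 × (1.960 + 1.282)² × 26² / 6² = 394.6, so 395 per arm and **790 in total**. This reproduces the plan. No figure is given for any subgroup or interaction.

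**2. Median split at N = 1000.** There are four cells of 250.
- SE of the difference in effects = 26 × √(4/250) = 3.29. The main-effect SE is 26 × √(4/1000) = 1.64.
- Detectable with 80% power: 2.80 × 3.29 = **9.2 points**.
- Power for a 6-point difference in effects: Φ(6/3.29 − 1.96) = 45%.

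**3. Full score at N = 1000** (normal score, linear modification).
- SE of the interaction per SD of pain = 2 × 26/√1000 = 1.64.
- Detectable with 80% power: 2.80 × 1.64 = 4.6 points per SD.
- The halves of a normal score differ in mean by 2√(2/π) = 1.596 SD, so this corresponds to 4.6 × 1.596 = **about 7.4 points** between halves.
- Power for a 6-point gap: 6/1.596 = 3.76 per SD; Φ(3.76/1.64 − 1.96) = about 63%.

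At N = 790 the detectable gaps are 10.4 and 8.3 points. Uneven arms inflate both SEs by the same factor. For an illustrative 600/400 split that factor is 1/(2√(0.6 × 0.4)) = 1.02, giving 9.4 and 7.5.

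**4. Information lost by splitting.** For a normal score cut so that a share q lies below, the fraction kept is φ(z_q)² / [q(1 − q)].

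| Score and cut | Loss |
|---|---|
| Normal, 50/50 | 36% (keeps 2/π = 0.637) |
| Normal, 40/60 | 38% |
| Normal, 30/70 | 42% |
| Normal, 20/80 | 51% |
| Assumed 0-10 score, mean 4 to 7, SD 2 to 2.5, cut at 6 or more | 33-46% |
| Uniform 0-10 score, central cut | 25% |

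A fair range is 25-50%, and more for extreme cuts.

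**5. Power under two true patterns.**

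| True pattern | Full score, linear term | Median split |
|---|---|---|
| Linear | 80% | 61% |
| Linear | 90% | 73% |
| Step exactly at the median | 61% | 80% |

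**6. Cut chosen after seeing the data.** Simulation with no interaction: 4,000 runs, N = 1000, assumed 0-10 score with mean 5.5 and SD 2.3, interaction tested at nominal 5%.

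| Cuts tried, most favourable reported | Type I error |
|---|---|
| One fixed cut (6) | 4.9% |
| Three (5 to 7) | 11% |
| Four (4 to 7) | 15% |
| Six (3 to 8) | 20% |

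**The case against.** **Thresholds and functional form often belong in an analysis plan, and none is shown.** This stands as far as it goes: the absent cut alone would be detail left to another document. What remains is that the protocol does state a method, a two-group contrast, and a more efficient one is available for data it already collects.

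**The scale is not stated.** This stands. A reader might take it as given that pain is recorded as a 0-10 score. The current text does not say so; the inference rests on the superseded version. If the item has only a few ordered categories, the figures above do not apply as they are.

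**The full-score analysis is not free.** A reader might infer that it is better without any drawback. It needs no new data, but a single linear term assumes linear modification. If the true pattern is a step at the median, the ranking reverses (61% against 80%), although the split has that advantage only when its cut falls on the step.

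**The inflated error rate is hypothetical.** A reader might infer that this analysis will run at 11-20%. Nothing in the documents plans a search over cuts. Nor does the missing threshold in the latest version show an intent to choose one late: the earlier threshold served another outcome, and a change between versions is no fault in itself.

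**The stakes are limited.** The trial was sized for a 6-point main effect. Even the full score has only about 63% power for a 6-point gap between halves, so the analysis is exploratory either way. The protocol does not rank its subgroup analyses, so this one should not be read as the main one. Nor does the text exclude an interaction test, and a two-group display is conventional and easy to read.

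**Conclusion.** The point holds as a cheap improvement, not as an error that threatens the trial. That the current text sets no cut for this subgroup needs no assumption to establish.

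The gain from the full score, a detectable gap of about 7.4 rather than 9.2 points, rests on five assumptions: a roughly normal numeric score, near-linear modification, a median cut, SD 26, and 1000 participants in equal arms. Other plausible score distributions and cuts put the information loss at 25-50%. The type I error figures describe what an unfixed cut would permit, not what is planned. The primary comparison and its sample size of 790, raised to 1000, are untouched.

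**What to change.** Amend the Subgroup analysis section and the matching registry field to:

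1. State the pain-intensity item and its scale.
2. Test a sheet × pain-intensity interaction using the full score in the linear model for PrepDM.
3. Report the JAMA minus ACHSQ difference with its 95% CI at one low and one high score, both fixed now.
4. Add a check with a flexible pain term, such as a quadratic or a spline, because a single linear term loses power if the true pattern is a threshold.
5. If a two-group display is kept, fix one cut before outcome data are examined and label the display descriptive.

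The cost is a few sentences of analysis wording, with no new data and no extra participants. Fixing the cut removes the scope for a data-driven choice; the full score recovers the precision if modification is near-linear.

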### Recruitment

Recruitment will happen from receipt of ethics approval (approximately April/May 2023) for a period of up to 12 months or until the target sample size of 1000 is achieved. Participants can opt in via the links on factsheets embedded in HealthShare consultation tools, or via an ad on social media.

GP users of the BetterConsult tool will be initially contacted about the interview/focus group study by email or newsletter from HealthShare. HealthShare regularly communicates with GP users of their tools in this way and have agreed to assist with recruitment. GPs who opt in to be contacted by investigators will receive an invitation email from the research team (Appendix E).

### Consent

Participants will access the survey via a QR code on a printed/emailed sheet, via a clickable link on the fact sheet page, or via a link in a social media advertisement. Once they click the link or scan the QR code, participants will be taken to an invitation page summarising the study, with a link to the full PIS which they can download. Those interested in proceeding will complete a digital version of the PCF. Only those clicking 'Yes' to on the digital PCF can access the survey.

GPs who agree to participate in an interview or focus group will receive a link to the participant information sheet and online consent form prior to the interview/focus groups.

### Data collection and storage

The survey responses will be collected via The University of Sydney Redcap (for the first two methods: patient-led and GP-led recruitment) and Qualtrics (for social media recruitment). Interviews and focus groups will be conducted and recorded on Zoom and transcribed using Zoom's transcribing feature and will be verified by a researcher. To deidentify Zoom recordings we will only download audio recordings without video. Audio recordings will be assigned a participant number with identifiers kept in a separate database in the University Research Data Store. Once the transcript is verified by the research team, the identifiable recording will be deleted.

Upon completion of the study all data will be stored in The University of Sydney Research Data Store (RDS)

## Appendix A – Social media advertisement

People who recently attended primary care for back pain needed for a study conducted by the researchers at the University of Sydney!

We want to hear your views about back pain fact sheets and intentions for future healthcare. The results will help us create better resources for GPs to use with patients who have low back pain. Participation involves a 10-min survey. [Click here](#) to find out more!

## Appendix B – Fact sheets

**COPYRIGHTED MATERIAL REDACTED**

Available from: <https://www.safetyandquality.gov.au/publications-and-resources/resource-library/how-manage-your-low-back-pain-information-patients>

## Appendix C

**COPYRIGHTED MATERIAL REDACTED**

Available from: <https://www.safetyandquality.gov.au/publications-and-resources/resource-library/how-manage-your-low-back-pain-information-patients>

## **Appendix D: Clinician interview/focus group guide**

Good morning/afternoon/evening. My name is \_\_\_\_\_ from the University of Sydney. I am conducting interviews/focus group to find out about GP views of back pain fact sheets.

Information from these interviews/focus group will help us understand the barriers and facilitators to implementation of fact sheet in primary care.

All of the information we collect in this interview/focus group will be kept confidential. The interview/focus groups will take about 30-60 minutes. I will also be audio-recording the interview/focus group so that I can concentrate on your responses and refer back to them during analysis. Is this okay with you?

If there are any questions you wish to skip or come back to at a later time, or if you need to take a break, please let me know.

Do you have any questions before we begin?

1. Can you tell me a little bit about your practice? [prompts listed below]
  - How many years have you worked as a GP?
  - Have you worked in both private and public sector?
  - What is the average consultation time per patient?
2. Which of the two back pain fact sheets do you prefer and why?
3. Which fact sheets do you think patient find easy to follow and why?
4. Which fact sheets do you think patient find difficult to follow and why?
5. What are the barriers to implementing the fact sheet?
  - Are they easily accessible to GPs?
6. What are the facilitators to implementing the fact sheet?
7. What are the strategies that will increase implementation of these fact sheets?

Thank you for making the time to speak with me.

Thank you again for your time. I wish to remind you that all the information you share with me today will be kept confidential.

## **Patient interview guide**

Good morning/afternoon/evening. My name is \_\_\_\_\_ from the University of Sydney. I am conducting interviews to find out about patient views of back pain fact sheets.

Information from these interviews will help us understand the barriers and facilitators to implementation of fact sheet in primary care.

All of the information we collect in this interview will be kept confidential. The interview should take no longer than 30 minutes. I will also be audio-recording the interview so that I can concentrate on your responses and refer back to them during analysis. Is this okay with you?

If there are any questions you wish to skip or come back to at a later time, or if you need to take a break, please let me know.

Do you have any questions before we begin?

1. Did you read the whole fact sheet?
2. Did you have any problem accessing the fact sheet?

#### Capability

3. What do you think of the fact sheet? Can you remember how you felt after reading the fact sheet? Did you know much about care for low back pain?
  - Was it easy or hard to follow?
4. Do you feel you know enough about what is recommended for managing back pain now?

#### Opportunity

5. Did you receive any advice or support from your GP about care for back pain? Did it influence your intention for medical care for back pain?
  - For scan, opioid, using heat, seeking massage/spinal manipulation, staying active
6. Did you feel reassured that there was no serious condition causing your back after reading the fact sheet?
  - What made you feel reassured/not reassured?

#### Motivation

7. What do you think would be better options to consider first (before scans/opioids) for back pain?

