[options: most / some / a little]
  - How would you rate the length of the fact sheet?  
[options: much too short / a little too short / just about right / a little too long / much too long]
  - How much of the information in the fact sheet was new to you?  
[options: all / most / some / none]
- The fact sheet talked about different ways to manage back pain. It mentioned **medical care (pain medicines, imaging, surgery)** and **non-medical care (massage, heat, staying active)** for back pain. Did you feel the fact sheet was: [options: leaning very much towards medical care/ leaning a bit towards medical care/Balanced/ Leaning a bit towards non-medical care/Leaning very much towards non-medical care]
- How strongly do you agree or disagree with each of the following statements.  
[options: strongly agree / agree / neither agree nor disagree / disagree / strongly disagree]
  - I found the information in the fact sheet clear and easy to understand.
  - I would recommend this fact sheet to other people who are considering their options to treat low back pain.
- Fidelity
  - How did you receive the fact sheet
    - From my GP
    - Via SMS from my GP practice
    - Social media
    - Other [please describe]
- Implementation

---

 Traeger AC et al. JAMA Neurol. 2019 Feb 1;76(2):161-169.

- We will also conduct semi-structured interviews and or focus groups (depending on feasibility) with up to 20 clinicians and 20 patients (interview only) to identify barriers and facilitators to implementation of the fact sheets in primary care. We used the COM-B framework to create our initial interview guide (Appendix D) which will be updated iteratively as interviews/focus groups progress. For the clinician focus groups if feasible, we will conduct up to 3 focus groups with 5-6 GPs in each group.
- Recruitment rates
  - Proportion of people exposed to the survey advertisement who consent to participate

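### The single Motivation question in the patient interview guide is leading, and no written question asks directly why a patient would or would not read or act on the fact sheet

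*Supplement*

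**What the plan says.** The latest protocol lists implementation among its secondary outcomes. It plans interviews or focus groups with up to 20 clinicians, and interviews only with up to 20 patients. Their purpose is "to identify barriers and facilitators to implementation of the fact sheets in primary care". The format is semi-structured, and on the guide the protocol says: "We used the COM-B framework to create our initial interview guide (Appendix D) which will be updated iteratively as interviews/focus groups progress".

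The introduction read to patients gives the same purpose: "Information from these interviews will help us understand the barriers and facilitators to implementation of fact sheet in primary care".

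The patient guide then has seven numbered questions. Two come before any heading; the rest fall under Capability, Opportunity and Motivation. Motivation holds only question 7: "What do you think would be better options to consider first (before scans/opioids) for back pain". No follow-up prompt is written beneath it.

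**The concern.** There are two separate difficulties with question 7.

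The first is its wording. It asks for better options and places them ahead of scans and opioids, so the ranking is supplied before the patient speaks. Someone who would choose a scan or an opioid first has to reject the premise to say so. Some patients will do that, but the wording pushes the other way. The push is the same whichever sheet was read, so answers may look like acceptance of non-scan, non-opioid care when they partly echo the question.

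The second is its subject. The interviews are about implementing the fact sheets, but question 7 asks which care a patient prefers and never mentions a sheet. If the rest of the guide does not ask why a patient wanted, or did not want, to read or use the sheet, the Motivation heading has no question aimed at the outcome it is meant to serve.

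**Working it through.** No arithmetic applies. The check is to read each patient question in Appendix D against the stated purpose and to compare the wording of question 7 with the protocol's other items on the same subject.

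**Coverage of the seven patient questions**

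| Question | Heading | Subject | Asks directly why the patient would or would not read or act on the sheet? |
|---|---|---|---|
| 1 | none | Whether the whole sheet was read | No; it records whether, not why |
| 2 | none | Problems with access | No |
| 3 | Capability | Opinion of the sheet, feelings after reading, prior knowledge, ease of following | No |
| 4 | Capability | Whether the patient now knows enough about recommended management | No |
| 5 | Opportunity | GP advice and its influence on intentions | No; it concerns the GP's advice |
| 6 | Opportunity | Reassurance after reading, and what produced it | No |
| 7 | Motivation | Which care options are better to consider first | No; the sheet is not mentioned |

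None of the seven asks it directly. The nearest are question 3, "What do you think of the fact sheet? Can you remember how you felt after reading the fact sheet", and question 6. Both may bring out reactions to the sheet that bear on motivation, but neither asks about wanting to read it or act on it.

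**Wording compared with the protocol's own items on scans and opioids**

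- *Survey items (Secondary outcomes, Management intentions).* Scans and opioids each have a neutral stem and five responses, running symmetrically from definitely will to definitely will not.
- *Interview question 5 (Opportunity).* After asking about GP advice, it continues: "Did it influence your intention for medical care for back pain". Scan and opioid are then listed as prompts beside heat, massage or spinal manipulation, and staying active, with no order of preference.
- *Interview question 7 (Motivation).* The ranking is built into the question, and scans and opioids appear only as what the better options precede.

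So the investigators used neutral wording twice for the same subject, and question 7 departs from it. Questions 3, 5 and 6 each have a written prompt beneath them; question 7 has none that would invite a different ordering.

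**Extent.** One of seven questions is affected, and it is the whole of one of the three headings, in up to 20 patient interviews. The direction of the push is clear from the wording. The documents give nothing from which to estimate its size.

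**The case against.** The strongest reply is that this is one prompt in a provisional topic guide and that contrary views have other ways out. Much of that stands.

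- Question 7 is open-ended and sits in a semi-structured interview, so the patient can reject the premise and the interviewer can probe. A reader might infer that the question cannot reveal contrary views. The documents do not support that: question 5 raises scans and opioids neutrally just before it, and the survey has balanced items on both. The registry update times the patient interview immediately after the survey, so both outlets come first. Question 5 is only a partial outlet, however, because it asks about the influence of GP advice rather than the patient's own order of preference.
- A reader might also infer that the Motivation component will have no usable data. That goes too far. Questions 1, 3 and 6 can yield some relevant material, as can the survey items on how much was read, length, balance and willingness to recommend. The protocol does not define what Motivation must cover, and a heading does not limit what patients say under it. What remains is narrower: no written question asks directly about wanting to read or act on the sheet.
- The guide is called initial and is to be updated as interviews progress. That makes a change easy but does not make it. No neutral or sheet-directed question is written, and patients interviewed before any update would get the leading one.
- Nothing in the protocol plans to report question 7 as evidence on care preferences; intentions are analysed from the survey. Misreporting is therefore a possibility and not part of the plan. Because any push applies equally to readers of both sheets, the wording gives no reason to expect a distorted comparison between them.

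**Conclusion.** The point holds as a minor one. Question 7 is leading on its face and may discourage contrary views. It does not address the fact sheet, and no other written patient question asks directly why a patient would or would not read or act on it, although implementing the sheets is the stated purpose of the interviews.

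The effect is confined to a secondary qualitative outcome. The PrepDM comparison, the sample size and the quantitative secondary outcomes are untouched. The conclusion assumes that interviewers put the question much as written; one who rephrases or probes freely would reduce the problem, but the guide does not script that.

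**What to change.** Before the first patient interview, use the updating the protocol already allows to make two changes under Motivation:

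1. Replace question 7 with a neutral form: *Which options would you consider first for your back pain, and why?* List scans and opioids as prompts on an equal footing with the other options, as question 5 does.
2. Add a question on the sheet itself: *What made you want, or not want, to read the fact sheet and act on it?*

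The cost is a wording change to the guide and about one extra minute per interview. If some interviews have already used the present wording, record which ones, so that their answers to question 7 can be read with that in mind.
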